## Abstract

**Background:**

Capecitabine and oxaliplatin (CAPOX) chemotherapy is a standard treatment for stage 2/3 colorectal cancer. Treatment is associated with dose-limiting toxicities such as neutropenia, vomiting, diarrhoea, and stomatitis. Short-term fasting prior to chemotherapy may help protect normal cells from the toxic effects of chemotherapy by allowing them to conserve energy for maintenance and repair. However, there is a lack of evidence to support the efficacy of short-term fasting in protecting against chemotherapy-related toxicities in humans, and it is not known whether people due to undergo chemotherapy will be willing and able to follow a short-term fast. Preliminary data confirming this is feasible are required before adequately powered trials can be designed and conducted.

**Methods:**

The short-term, water only, fasting trial (SWiFT) is a two-armed feasibility randomised controlled trial, aiming to recruit 30 people scheduled to begin routine treatment with CAPOX chemotherapy for stage 2/3 colorectal cancer. Participants will be randomly allocated, in a 1:1 ratio, to either a 36-h fast or standard dietary advice prior to chemotherapy administration for the first 3 cycles of chemotherapy. The primary outcome measures will assess the feasibility of the trial and include: adherence to intervention, recruitment, retention, and data completion rates as well as the acceptability of the intervention which will be qualitatively assessed. The secondary outcome measures aim to provide further information on possible outcomes of interest for a definitive trial and include side effects of chemotherapy, quality of life, markers of cellular metabolism and inflammation, appetite, and sarcopenia.

**Discussion:**

It is not known whether it is possible to recruit to a trial of short-term fasting in this population, or whether participants would be able to adhere to the intervention. Therefore, we aim to test the feasibility of a pre-chemotherapy, 36-h, water-only fast in people receiving CAPOX chemotherapy for stage 2/3 colorectal cancer.

**Trial registration:**

This trial has been registered with the ISRCTN Registry. Trial registration no: ISRCTN17994717. Date of registration: 23 October 2018. URL: http://www.isrctn.com/ISRCTN17994717

## Background

During times of nutrient scarcity, normally functioning body cells have the ability to switch from a state of growth and development to a state of maintenance and repair, which enables cells to conserve energy [1, 2]. This process is mediated in part by a reduction in glucose, insulin, and IGF-1 (Insulin-like growth factor-1) which in turn alters cellular pathways, reducing activation of those involved in cell proliferation and growt h[2, 3].

Conversely, as cancer is a disease of uncontrolled cell growth, genetic mutations in tumour cells enable them to continue to proliferate, even when nutrients are scarc e[4]. This is due to loss-of-function mutations in tumour-suppressor genes (Rb, p53, and PTEN) which lead to insensitivity to growth-inhibitory signals. In addition, mutations in oncogenes (Ras, Akt, and mTOR) activate proliferation pathways, even in the absence of growth signal s[3].

This difference between healthy and tumour cells in response to food restriction has been coined “Differential Stress Resistance (DSR)”. Pre-clinical research in animal models suggests that DSR could be exploited during chemotherapy to limit the toxic effects of chemotherapy in healthy cells, while leaving tumour cells susceptible to treatment [5].

The exact mechanisms behind DSR are not fully understood. It is believed they may be partially mediated by the reduction in blood glucose and growth factors such as Insulin-like Growth Factors (IGFs) brought about by fasting. Within healthy cells, this negatively regulates downstream cellular pathways such as the Ras/MAPK and P13K/Akt pathways which are promoters of cellular proliferation [3]. This allows the cells to cease growth and convert energy to cell maintenance.

Another mechanism through which DSR may protect healthy cells is through increased autophagy. Calorie restriction activates the enzyme “AMP activated protein kinase” which increases autophagy. Autophagy can target defective organelles to be degraded into substrate for use in energy production and repai r[3]. Cancer is often associated with a defect in autophagic capacity as oncogenes Akt and P13k inhibit autophagy while the tumour suppressor gene PTEN, which loses function in tumour cells, would usually upregulate it. The decrease in growth factors associated with fasting may therefore lead to the upregulation of autophagy in normal cells but not in cancer cells, allowing them to degrade organelles for energy us e[6].

Although some studies of fasting during chemotherapy in cell lines and animal models have shown promising results, it is unclear how well these findings translate to human s[3, 7, 8].

To date, two early-stage trials on short-term fasting during chemotherapy have been completed: A pilot trial in 13 people with breast cance r[9] and a dose-escalating safety and feasibility trial in 20 people receiving platinum-based chemotherapy for any cancer typ e[10]. These studies show fasting up to 72hrs around the time of chemotherapy administration to be safe and feasible; however, the 72hour fast may have been subject to poorer adherence. There was some evidence of reduced haematologic toxicities between groups, but limited evidence of differences between groups for other chemotherapy side effects. However, these trials were not powered to provide evidence of differences in toxicities between groups, so the results should be treated as preliminary findings that require replication in adequately-powered studies.

No trials have been conducted to date in people receiving chemotherapy for colorectal cancer. A standard treatment in the UK for stage 3 colorectal cancer (or stage 2 colorectal cancer that is at high risk of local recurrence) is surgical resection, followed by Capecitabine and Oxaliplatin (CAPOX) chemotherapy [11]. Dose-limiting toxicities for this combined regimen include vomiting, diarrhoea, and stomatitis [12]. When used within an RCT, withdrawal rates on CAPOX due to adverse events were 21% [13]. Therefore, interventions which aim to limit toxicities in this treatment group are of interest. This identifies colorectal cancer as an understudied cancer site in terms of fasting to induce DSR as a means of reducing chemotherapy toxicities.

## Methods

### Trial aim and design

Patient and public involvement were used to inform the design of SWiFT. It is a two-armed randomised controlled feasibility trial. 30 people scheduled to begin routine treatment with CAPOX chemotherapy for stage 2/3 colorectal cancer will be randomly allocated, in a 1:1 ratio, to either a 36-hour fast or standard dietary advice, to be implemented prior to each of the first three treatment cycles.

The aim of the study is to determine whether a trial of a 36-hour pre-chemotherapy fast is feasible in people receiving CAPOX chemotherapy for stage 2/3 colorectal cancer.

### Outcome measures

The primary outcome measures assess the feasibility of this trial. These are

#### Recruitment rates

Calculated as the percentage of eligible patients recruited each month, as recorded in the recruitment logs at each site.

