### Participants

The feasibility study will aim to recruit 30 participants from two NHS hospital sites in the West of England. Recruitment will take place between September 2019 and September 2020. As this is a feasibility trial, it is not appropriate to perform formal power calculations. Instead a sample size of 30 was chosen based on the practicalities of conducting an early-stage intervention trial within the scope of a Ph.D. project. This sample size will also allow for the estimation of parameters for potential primary outcomes in a definitive trial, helping to inform future sample size calculations [23].

Eligible participants will provide written informed consent, taken by a member of the site-based research team. Participants will be deemed eligible if they are aged ≥ 18 years with histologically confirmed stage 2/3 colorectal cancer, are due to undergo treatment with adjuvant CAPOX chemotherapy, have an ECOG performance status ≤ 2 and are able to provide written informed consent. People will be excluded if they have a clinical diagnosis of cachexia or diabetes, a body mass index (BMI) ≤ 18.5 kg/m^2^, history of an eating disorder, or drug/alcohol abuse are participating in another study that may affect the outcomes of this feasibility trial or are unable to speak/understand English.

Treatment discontinuation will be at the discretion of the principal investigator or other attending clinician or the participant themselves. All participants who withdraw from the trial intervention will be followed up as per the follow-up schedule until trial completion. The exception to this will be if a participant explicitly withdraws consent for any further trial follow-up.

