### Quantitative data analysis

Rates and confidence intervals will be reported for the primary outcomes. Baseline characteristics in each trial arm will be reported. Secondary outcome data will be summarised using means (standard deviations) or medians (inter-quartile ranges) as appropriate for continuous variables, and frequencies with percentages (n, %) for categorical variables, to inform outcomes of interest and sample size calculations in future trials. All quantitative data will be analysed in STATA 15 [24].

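### The recruitment outcome is defined only as a monthly percentage of eligible patients; at two to three recruits a month each value is nearly uninformative, and the percentage does not report accrual speed

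*Protocol article*

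**What the plan says.** All references are to the protocol article.

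- **Outcome measures.** The primary outcomes are feasibility outcomes: "The primary outcome measures assess the feasibility of this trial". Recruitment is the first one listed.
- **Recruitment rates.** The whole definition is one sentence: "Calculated as the percentage of eligible patients recruited each month, as recorded in the recruitment logs at each site".
- **Quantitative data analysis.** "Rates and confidence intervals will be reported for the primary outcomes". Neither the level nor the method of the interval is given, which is normal for an article.
- **Participants.** The target and the number of sites are stated: "The feasibility study will aim to recruit 30 participants from two NHS hospital sites in the West of England". The size is pragmatic: "Instead a sample size of 30 was chosen based on the practicalities of conducting an early-stage intervention trial within the scope of a Ph.D. project". The same section gives the calendar window: "Recruitment will take place between September 2019 and September 2020".

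The article defines no whole-period percentage and no measure of participants per month or per site per month. It gives no expected number of eligible patients.

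**The concern.** The definition fixes a numerator, a denominator and a time unit. The numerator and denominator give uptake, that is, the share of eligible patients who join. The time unit cuts that share into calendar months, and in a trial of this size each month holds only a handful of patients.

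The heading speaks of rates and the definition is monthly, which suggests that speed was also of interest. A percentage does not carry speed: 1 of 2 and 10 of 20 eligible patients are both 50%, yet the second is ten times the accrual.

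The discussion in the abstract names the possibility of recruiting in this population as one of two unknowns behind the trial. Planning a later trial calls for both uptake with reasonable precision and recruits per site per month. Followed literally, the definition reports neither directly.

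**Working it through.** **Plan's own figure.** There is none to reproduce. The 30 is a practical choice with no power or precision target, so the check is of precision.

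**Inputs from the article.** 30 participants; two sites; September 2019 to September 2020, which is 12 months, or 13 calendar months if both Septembers count.

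**Assumption.** The number eligible is not given. An overall recruited share of 20% to 70% is assumed, so the number eligible is 30/0.20 = 150 down to 30/0.70 ≈ 43.

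**Step 1: recruits per unit.**
- Per month: 30/12 = 2.5; 30/13 = 2.31.
- Per site per month: 30/24 = 1.25; 30/26 = 1.15.

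**Step 2: eligible patients per month.** From 43/13 = 3.3 to 150/12 = 12.5.

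**Step 3: interval for one month.** Exact (Clopper–Pearson) 95% limits for x of n are the 0.025 quantile of Beta(x, n−x+1) and the 0.975 quantile of Beta(x+1, n−x).

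| Month | Percentage | Exact 95% CI | Width (points) |
|---|---|---|---|
| 2 of 3 | 67% | 9–99% | 90 |
| 2 of 4 | 50% | 7–93% | 86 |
| 3 of 6 | 50% | 12–88% | 76 |
| 3 of 8 | 37.5% | 8.5–75.5% | 67 |
| 3 of 12 | 25% | 5.5–57% | 52 |

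**Step 4: empty cells.** With Poisson arrivals, the chance of no recruits is exp(−mean).
- Month: exp(−2.5) = 8% to exp(−2.31) = 10%.
- Site-month: exp(−1.25) = 29% to exp(−1.15) = 32%.
- If 43 to 60 patients are eligible in total, the chance that a site-month has nobody eligible is exp(−60/24) = 8% to exp(−43/26) = 19%. A by-site monthly percentage is then undefined.

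**Step 5: the same counts pooled over the period.**

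| Pooled | Percentage | Exact 95% CI |
|---|---|---|
| 30 of 150 | 20% | 14–27% |
| 30 of 100 | 30% | 21–40% |
| 30 of 60 | 50% | 37–63% |
| 30 of 43 | 70% | 54–83% |

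These intervals are about 13 to 29 points wide, against about 50 to 90 for a single month.

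**Step 6: accrual if 30 are recruited.** Exact Poisson limits for 30 events are χ²(0.025; 60)/2 = 20.24 and χ²(0.975; 62)/2 = 42.83.
- Over 24 site-months: 30/24 = 1.25, 95% CI 20.24/24 to 42.83/24 = 0.84 to 1.78.
- Over 26 site-months: 30/26 = 1.15, 95% CI 20.24/26 to 42.83/26 = 0.78 to 1.65.

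**The case against.** The strongest reply is that the definition may only name the unit in which the logs are tabulated. Nothing in the article says that a separate interval will be computed for each month, and nothing rules out a whole-period percentage. The logs must hold the recruited and eligible counts, and the article gives the sites and the window, so both pooled uptake and accrual can be worked out afterwards. Uptake answers directly whether patients are willing to join. What the article says about informing a later trial concerns sample size and outcome variance, not the number of sites or the duration. The interval method and by-site layout belong in an analysis plan.

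Much of this stands. It limits the point to the definition: no information is lost and nothing in the article is contradicted. The choice of interval method is not a finding. But the monthly unit is stated text, not a detail left to another document, and it is the only definition of this primary outcome. Neither it nor the analysis section commits to a pooled figure or an accrual figure. That both can be recovered shows that the repair is cheap, not that the definition is adequate.

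**Conclusion.** The point holds as a badly chosen unit for a primary outcome. Each monthly percentage would carry an interval about 50 to 90 points wide, and accrual speed is not part of the stated measure. This holds across the assumed 20% to 70% recruited share. The accrual figures assume that the target of 30 is met, that both sites are open throughout, and that arrivals follow a constant Poisson rate.

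Three stronger readings are not supported:

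- A reader might infer that uptake is too sparse to estimate in this trial. Sparsity affects single months only; the pooled intervals in step 5 are usable.
- A reader might infer that the trial cannot yield accrual speed. That is true of the percentage taken alone, but the logs hold the counts.
- A reader might infer that a monthly figure can exceed 100%. This happens only if recruits are counted by consent date and eligible patients by the date found eligible. The article does not say so, and on the natural reading the recruited are a subset of the eligible.

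**What to change.** Replace the single definition with two measures:

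1. **Uptake:** number randomised divided by number eligible over the whole recruitment period, with a 95% confidence interval.
2. **Accrual:** number randomised per site per month open, with a Poisson 95% confidence interval.

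Keep the monthly counts or percentages as description only, without intervals. If they are shown, state which event date places a patient in a month, so that numerator and denominator refer to the same patients.

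The cost is a change of wording. The counts come from the existing recruitment logs; the only other item needed is the dates on which each site opened and closed to recruitment. Sample size, visits and participant data collection are unchanged.

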#### Adherence to intervention

Assessed by analysis of self-reported food logs, completed by participants during the 36-h fast. Participants will be considered to have adhered to the fast if they consume less than 14% of their basal metabolic rate (BMR) requirements (kcal/day calculated using the Oxford equations for BMR [14]), in the 36 h prior to chemotherapy administration. This equates to approximately 200 kcal per day, depending on age and gender. The aim of using a cut-off of 14% BMR is to allow participants to consume small amounts of food if they need to mitigate any side effects of fasting, while keeping the participant in the metabolically altered state associated with fasting. This cut-off has been used in previous trials of fasting [10]. To encourage participants to only consume a small number of calories, a list of 50 kcal snacks will be provided. The percentage of adherent participants will be reported for each cycle. Reasons for non-adherence will also be recorded.

#### Retention rates

Calculated as the number of participants who completed data collection for each fasting cycle (both self-reported data and clinical care team recorded data associated with that cycle) divided by the number of participants randomised.

#### Acceptability and tolerability of the intervention

Qualitatively assessed through in-depth semi-structured interviews with trial participants.

#### Data completion rates

Completeness of data will be assessed for all measures at each cycle. The secondary outcome measures aim to provide further information on possible outcomes of interest in a definitive trial. Including these in the feasibility trial will allow for the data collection methods to be assessed as well as providing information on the variance of each outcome. The impact of fasting on these measures could then be tested in a suitably powered trial. The secondary outcome measures are:

#### Side effects of chemotherapy

Measured using the Patient-Reported Outcomes version of the Common Terminology Criteria for Adverse Events (PRO-CTCAE™) [15], Full-blood count (FBC) and blood chemistry analysis. Short-term dietary fasting may result in differential stress resistance between normal and tumour cells, which may render tumour cells more susceptible to chemotherapy than normal cells. Patient-reported side effects will be collected on day 1 of each cycle (prior to chemotherapy administration) and at home on days 3 and 7 (via participant-completed questionnaires) to capture the transient nature of side effects. Data will also be recorded on whether participants completed their first 3 cycles of chemotherapy and reasons for dose reductions/delays/early termination if they occurred.

#### Quality of Life

Measured using the EQ-5D-5L health-related quality of life instrument [16]. This would be used to explore whether fasting or its impact on chemotherapy side effects, increases quality of life (QoL).

#### Haematologic toxicities

Assessed using routine FBC data collected prior to each round of chemotherapy and classified according to CTCAE criteria [17].

#### Markers of cellular metabolism

Measures will include glucose, insulin, IGF-I, IGF-II, IGF-binding protein (IGFBP)-2 and IGFBP-3. These will be used to study the effect of the fast on markers of cellular metabolism. They will also be considered in conjunction with self-reported dietary intake to explore adherence to the intervention, as the level of these markers would be expected to be reduced in adherent participants. Baseline samples will be collected prior to fasting when participants attend for routine pre-chemotherapy blood tests (approx. 4 days prior to cycle 1). Follow-up samples will be collected immediately prior to chemotherapy administration at cycles 1 and 3.

#### Markers of inflammation

C-reactive protein (CRP) will be measured at baseline (pre-fast) and prior to chemotherapy administration at cycles 1 and 3. In a full-powered trial, this would be used to explore whether fasting reduces inflammation.

#### Appetite

Self-reported on visual analogue scales [18]. As chemotherapy can alter taste and appetite [19], measuring appetite is of interest to explore whether fasting negates reduced appetite through decreased treatment side effects.

#### Sarcopenia

Assessed using computerised tomography (CT) and handgrip dynamometer [20]. Single axial images of the third lumbar (L3) level muscle mass, taken from pre-chemotherapy staging and follow-up CT scans conducted as part of routine care, will be analysed for body composition using SliceOMatic software [21]. Handgrip strength will be measured three times in the dominant hand, while the participant is in a seated position, arms supported at right angles, and feet on the floor. Measurements will be taken by the research site’s clinical trial officer/research nurse who will be trained in following the trial’s standard operating procedure for measuring handgrip strength. The mean of the three measures will be used to assess handgrip strength, using cut-off values defined by the European Working Group on Sarcopenia in Older People (EWGSOP) to identify low grip strength [22]. These measures will allow us to inform future trials on the prevalence of sarcopenia in this population and explore the safety of fasting in relation to this condition.

### Participants

The feasibility study will aim to recruit 30 participants from two NHS hospital sites in the West of England. Recruitment will take place between September 2019 and September 2020. As this is a feasibility trial, it is not appropriate to perform formal power calculations. Instead a sample size of 30 was chosen based on the practicalities of conducting an early-stage intervention trial within the scope of a Ph.D. project. This sample size will also allow for the estimation of parameters for potential primary outcomes in a definitive trial, helping to inform future sample size calculations [23].

Eligible participants will provide written informed consent, taken by a member of the site-based research team. Participants will be deemed eligible if they are aged ≥ 18 years with histologically confirmed stage 2/3 colorectal cancer, are due to undergo treatment with adjuvant CAPOX chemotherapy, have an ECOG performance status ≤ 2 and are able to provide written informed consent. People will be excluded if they have a clinical diagnosis of cachexia or diabetes, a body mass index (BMI) ≤ 18.5 kg/m^2^, history of an eating disorder, or drug/alcohol abuse are participating in another study that may affect the outcomes of this feasibility trial or are unable to speak/understand English.

Treatment discontinuation will be at the discretion of the principal investigator or other attending clinician or the participant themselves. All participants who withdraw from the trial intervention will be followed up as per the follow-up schedule until trial completion. The exception to this will be if a participant explicitly withdraws consent for any further trial follow-up.

